### Data collection

Data will be collected at three time-intervals, baseline pre-intervention (T1), 42 weeks (T2), and 84 weeks after the interventions begin (T3). The RAs, who are blinded to group allocation and not involved in interventions, will collect the data in the GOPCs in T1, and *via* telephone call in T2 and T3. They will be tested on inter-rater reliability to ensure data quality. Five percent of the data will also be randomly selected for independent review. Participants will receive a HK$ 50 coupon as a token of appreciation for their time commitment and to help cover transportation costs upon completion of the T3 data collection.

Semi-structured interviews will be carried out in T3 by research team members. A one-time in-depth focus group interview allows the research team to understand the group dynamics where different opinions from persons can be explored. During the interview, participants will be asked questions such as "What is your experience with the telecare consultation?" and "What aspects of the intervention program do you like or dislike?" At each time point, separated interviews will be conducted to the same group of people including (1) GOPC manager, (2) clinic healthcare providers (i.e. doctor, nurse), and (3) 64 (20%) of the patients in telecare group.

### Data analysis

The Statistical Package for Social Sciences version 26 software will be used to analyse the quantitative data. The independent samples t-test will be used to calculate the difference between the alternate telecare and face-to-face consultation usual face-to-face consultation groups, and the null hypothesis will be rejected if the upper bound of the 95% 1-sided confidence interval is smaller than the non-inferiority margin, which sets at 0.4%. Regression using two-way interactions between the study group (telecare versus conventional) and a range of demographic data such as age, gender, and diabetes type and duration will be performed to examine the subgroup effects.

The principles of thematic analysis will be used to analyse the qualitative data gathered in the semi-structured interviews. All focus group interviews will be audio-recorded and transcribed. The research team members will independently examine the raw text and identify relevant themes. The team will discuss and construct a framework for analysis with clearly defined codes and categories, which will help in summarizing the data in order to answer the research questions. An audit trail will be kept to ensure consistency in the coding and interpretation, and all discrepancies will be resolved by consensus.

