### Study setting, subjects and recruitment strategies

The study will be implemented in seven government out-patient clinics (GOPCs) under Hospital Authority in the New Territories West Cluster from Jan 2023 to Dec 2025. The subjects who are DM patients (either type 1 or type 2) with regular follow-up appointment in the clinic will be screened and recruited into the study if they 1) are aged 18 or above, and 2) have a confirmed diagnosis of diabetes. They will be excluded if they are 1) having dementia, 2) having unaccompanied hearing or visual loss, 3) not living in an area with Internet coverage.

Research assistants (RAs) will introduce the program to the eligible DM patients in the clinics. For those who are eligible and agreed to join, RAs will collect their signature for the consent form and baseline data. After successfully collect their data, the RAs will call the principal investigator (PI) of the research team for randomization. The PI will put the numbers (i.e. 1 = “telecare group”, 2 = “control group”) that generated from a software “Research Randomizer” into sealed envelopes and open sequentially when receive the call from RAs. A block randomization of size 8 will be employed to ensure balanced representation of the subjects in each group. The PI will provide the group list to the clinic clerk, who will then inform individual participants about their randomization results and guide them to follow the assigned delivery consultation mode. The Research Assistants (RAs), who will solely be involved in data collection, and the statistician, who will be responsible for data analysis, will be blinded to the group assignment.

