### Sample size

Power analysis is used to estimate the sample size of the study. Based on the non-inferiority criteria of 0.4% between the two groups on the primary outcome, HbA1c, in a previous similar study [22], and the varying drop-out rates of previous studies, which ranged from 0% to 20% over a follow-up period of 1–10 years [23–26], assuming a 20% of beta error, a 0.05 of alpha level, and a drop-out rate of 20% in this study, a sample size of 350 subjects will be needed in each group, i.e. a total of 700 subjects in two groups.

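### The primary HbA1c non-inferiority test is a valid but unadjusted t-test; adding baseline HbA1c as a covariate would narrow the interval and reduce exposure to chance imbalance at no cost

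*Protocol article*

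**What the plan says.** The Data analysis section of the protocol article fixes both the test and the decision rule. On the test: "The independent samples t-test will be used to calculate the difference" between the telecare group and the usual-care group. On the rule: "the null hypothesis will be rejected if the upper bound of the 95% 1-sided confidence interval is smaller than the non-inferiority margin", which is set at 0.4%. No covariate is named. The only regression described is a set of interactions between study group and demographic variables, meant for subgroup effects.

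Baseline HbA1c is nevertheless available. The Data collection section schedules measurement at baseline (T1), 42 weeks (T2) and 84 weeks (T3), and the Discussion says that HbA1c will be measured and compared at all three. The recruitment section places baseline data collection before the call for randomisation. It describes blocks of 8 and no stratification by HbA1c. Under Effectiveness, background demographic data are gathered to compare the arms at baseline; adjustment is not mentioned.

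The Data analysis section does not say whether the t-test applies to follow-up HbA1c or to change from baseline.

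**The concern.** The primary conclusion depends on where one upper confidence limit falls against a fixed margin of 0.4. Two things can be improved.

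- **Precision.** The part of the follow-up variation that baseline HbA1c predicts stays in the error term of a t-test on follow-up values. The bound then lies further from the estimate than it need, and a telecare programme that is truly non-inferior is more likely to miss the margin.
- **Chance imbalance.** Eligibility covers type 1 and type 2 diabetes with no HbA1c range, and the randomisation described does not balance HbA1c. If the arms differ at baseline by chance, part of that gap carries into the unadjusted follow-up difference. It can favour or penalise telecare in the one trial that will be run.

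**Working it through.** **Inputs from the documents**

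- Margin: "Based on the non-inferiority criteria of 0.4% between the two groups on the primary outcome, HbA1c" (Sample size).
- Error rates and loss: "assuming a 20% of beta error, a 0.05 of alpha level, and a drop-out rate of 20% in this study" (Sample size). Sidedness is not stated there; the rule in Data analysis is one-sided 5%.
- Size: "a sample size of 350 subjects will be needed in each group, i.e. a total of 700 subjects in two groups" (Sample size). After 20% loss, 350 × 0.8 = 280 evaluable per arm.

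**Assumptions, not in the documents**

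- SD of HbA1c: not given, so back-calculated below.
- Baseline to follow-up correlation r: not given, so shown for 0.3, 0.5 and 0.7.
- True difference zero, and equal SD at baseline and follow-up.

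**Step 1. The plan's own figure.** With no SD, 350 per arm cannot be reproduced directly. Solving n = 2·SD²·(z_α + z_β)²/0.4² for SD at n = 280:

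- one-sided 5%: SD = 0.4 × √(280/2) / (1.645 + 0.842) = 1.90
- one-sided 2.5%: SD = 0.4 × √(280/2) / (1.960 + 0.842) = 1.69

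Forward check: SD 1.90 gives 279 per arm, or 349 after allowing for loss. SD 1.69 at one-sided 2.5% gives 281, or 352.

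**Step 2. Precision if follow-up values are tested.** ANCOVA multiplies the SD by √(1 − r²), whatever the SD. The distance from estimate to upper bound is 1.645 × SD × √(2/280) × √(1 − r²). Power is Φ(0.4 / [SD × √(2/280) × √(1 − r²)] − 1.645).

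| | t-test | r = 0.3 | r = 0.5 | r = 0.7 |
|---|---|---|---|---|
| Width relative to t-test | 1 | 0.954 | 0.866 | 0.714 |
| Distance to bound, SD 1.90 | 0.264 | 0.252 | 0.229 | 0.189 |
| Power, SD 1.90, one-sided 5% | 80% | 83% | 89% | 97% |
| Power, SD 1.69, one-sided 5% | 88% | 90% | 94% | 99% |
| Enrolled per arm for 80% power, SD 1.90 | 349 | 318 | 263 | 179 |

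**Step 3. Chance imbalance.** The standard error of the baseline difference is SD × √(2/280): 0.143 at SD 1.69 and 0.161 at SD 1.90. Its 95% range is ±0.28 to ±0.32. A baseline gap shifts the expected unadjusted follow-up difference by r times the gap. At the edge of the range:

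- SD 1.69, r = 0.5: 0.5 × 0.280 = 0.14, and 0.14/0.4 = 35% of the margin
- SD 1.90, r = 0.7: 0.7 × 0.315 = 0.22, and 0.22/0.4 = 55% of the margin

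**Step 4. Type I error.** In a simulation of 20,000 trials (SD 1.69, r = 0.6, 280 per arm, true difference equal to the margin), non-inferiority was wrongly declared in 4.8% by the t-test and 5.2% by ANCOVA, both close to the nominal 5%. Among trials in which telecare started more than one standard error lower by chance, the rates were 18.6% and 5.2%. Where it started more than one standard error higher, they were 0.1% and 5.8%.

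**Step 5. If change from baseline is tested instead.** Relative to follow-up values, the SD of change is √(2(1 − r)).

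| | r = 0.3 | r = 0.5 | r = 0.7 |
|---|---|---|---|
| Change score | 1.18 | 1.00 | 0.77 |
| ANCOVA | 0.95 | 0.87 | 0.71 |

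ANCOVA is the more precise at each value, but at r = 0.7 the gap is small.

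**The case against.** The strongest reply is that nothing is broken. Under randomisation the t-test is unbiased, Step 4 confirms its overall error rate, and chance imbalance is already allowed for in the unadjusted interval. If the unstated SD is right, the test also delivers the planned 80% power. All of this stands. A reader might infer from the imbalance argument that the planned analysis is biased or inflates the type I error; it does neither. The 18.6% in Step 4 is conditional on an unlucky allocation and is offset by the near-zero rate on the other side.

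A reader might also set the baseline gap directly against the margin. At SD 1.90 a gap above 0.2, half the margin, arises in about 21% of trials. That overstates the effect, because only r times the gap reaches the outcome. A shift above 0.2 needs a gap above 0.2/r, which occurs in about 0.2%, 1.3%, 3.8% or 7.5% of trials at r = 0.4, 0.5, 0.6 or 0.7.

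Nor can it be said that baseline is certainly ignored. A t-test on change would use it in part, the figures in Steps 2 and 3 would then not apply, and the back-calculated SD would be that of change. Step 5 shows that a smaller advantage for ANCOVA remains.

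Finally, an article condenses its protocol, and covariate lists are often left to an analysis plan. Here, however, the article names the primary test and its decision rule, so the choice itself can be reviewed. The objection does hold for clinic terms: "The study will be implemented in seven government out-patient clinics (GOPCs) under Hospital Authority", but no clinic effect is given from which to judge the benefit of adjusting for it.

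**Conclusion.** The point holds as one of efficiency and robustness. The stated primary test is valid, but it leaves precision unused that the trial has already paid to collect.

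If follow-up values are tested, adjustment narrows the interval by about 5% to 29% for r of 0.3 to 0.7, independently of the SD. The power gain, from 80% to between 83% and 97%, depends further on the back-calculated SD of 1.90 and on 280 evaluable patients per arm. If the sample size was set at one-sided 2.5%, the implied SD is 1.69, and power under the stated one-sided 5% rule starts at 88%, so there is less to gain. At the low end of r the benefit is modest. The documents do not show where r lies.

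That adjustment helps is certain in direction; its size is not. A stricter alpha is a separate question and does not follow from this point.

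**What to change.** In Data analysis, make the primary estimate the telecare minus control difference in HbA1c from an ANCOVA with T1 HbA1c as covariate, or from a mixed model that uses T2 and T3 with the same covariate. Compare the same one-sided 95% upper bound with the same 0.4% margin. Keep the t-test as a sensitivity analysis, and state whether it uses follow-up values or change. Apply the same baseline adjustment to the continuous secondary outcomes: BMI, lipids, medication adherence and the SF-12 component scores. A clinic term is optional.

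Fix this before any unblinded analysis, so that the choice of covariate cannot depend on the results. The cost is a sentence or two of text: no new data, no new patients and no change to the margin or alpha.

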#### Operation phase

Both intervention (alternate telecare and face-to-face consultation) and control (usual face-to-face consultation) group subjects will receive DM RAMP in one of the seven GOPCs. Patients enrolled in the RAMP will undergo an initial risk assessment, which include physical examination, eye and foot assessment, laboratory testing, and complication screening. According to their conditions, the healthcare providers, including nurse, practitioners, and physiotherapists, will provide individualized diabetes education and lifestyle modification advice to the DM patients [21]. In this study, the healthcare providers for both groups will be the same to minimize the operator effect. The only difference in these two groups is the delivery model, where intervention group will receive alternate telecare and face-to-face consultations and control group will receive usual face-to-face consultations only within the 84-week study period. During this program duration, there will be a total of seven consultations for both groups as each consultation is approximately 14 weeks apart. Both groups will receive the first consultation onsite. Before the end of the first consultation, the healthcare providers will provide intervention group patients instructions on how to use HA Go, a telecommunication app that can provide virtual face-to-face service, in their next meeting. A clerk will help contact the patients one hour prior to the next consultation for rehearsal. Any technical problems will be managed in this one hour by either the clerk or the IT team.

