#### Effectiveness:

The effectiveness outcomes of the program include HbA1c, fasting lipid profile, body mass index (BMI), medication adherence, quality of life (QoL), and health service utilization. The primary effectiveness outcome of this study is the HbA1c level. HbA1c is a standard assessment of glycemia and refers to the mean blood glucose levels over the previous 2 to 3 months [27]. Fasting lipid profile includes cholesterol level, and high- and low-density lipoprotein. Similar to HbA1c, the fasting lipid profile will be drawn from patients’ blood when the patient has onsite consultation. The results can be extracted from the hospital database. BMI will be measured each time during GOPC admission by dividing weight in kilograms by height in meters^2^. Medication adherence will be measured by adherence to refills and medication scale [28]. This 4-point Likert scale has scores range from 12 to 48, with lower scores representing better medication adherence. The scale has demonstrated high internal consistency, with a Cronbach’s alpha of 0.81 [28]. Quality of life will be evaluated by the version 2 of the 12-item Short Form Health Survey [29]. The scale measures various aspects of physical and mental health from which physical and mental component scores can be summed. It has been widely used in Chinese diabetic patients with good validity and reliability [30,31]. The outcomes of health services utilisation include the total number of unscheduled visits to general out-patient departments, general practitioners (GP), emergency departments, and hospitals, and the total health service attendance. The information will be extracted from the hospital database, except for GP visits, which will be reported by the subjects.

Background demographic data will be collected to compare the baseline differences between the two groups. They include age, gender, marital status, education, work status, years of using a smartphone, financial status, family living in the same household, caretaking support, diabetes type and duration, date of first follow-up, number of referrals, professionals to whom the patient is referred.

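### The stated primary t-test cannot use the baseline and interim HbA1c that the trial collects, so missing final values that relate to HbA1c differently in the two arms would bias the non-inferiority result

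*Protocol article*

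**What the plan says.** The Data analysis section names the method for the non-inferiority comparison: "The independent samples t-test will be used to calculate the difference" between the two consultation modes. The decision rule is that the "null hypothesis will be rejected if the upper bound of the 95% 1-sided confidence interval is smaller than the non-inferiority margin", set at 0.4%. The section names no decision visit, baseline covariate or repeated-measures term for this comparison.

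The Sample size section gives the planning values: "Based on the non-inferiority criteria of 0.4% between the two groups on the primary outcome, HbA1c", then "assuming a 20% of beta error, a 0.05 of alpha level, and a drop-out rate of 20% in this study", from which "a sample size of 350 subjects will be needed in each group".

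Other sections show that HbA1c is repeated. The Data collection section sets time points at baseline (T1), week 42 (T2) and week 84 (T3), and the Discussion says HbA1c is compared at all three. The Effectiveness section says that samples are taken from the patient's "blood when the patient has onsite consultation" takes place, and that results can be extracted from the hospital database. The Operation phase section schedules seven consultations, the first onsite for everyone, and "each consultation is approximately 14 weeks apart". The Maintenance section says withdrawals and changes of mode will be counted with reasons.

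**The concern.** The method named is a two-sample comparison of one value per patient. Whatever the analysis set, it cannot use what a patient's baseline or interim HbA1c says about a missing final value. Run on observed values, it is unbiased only if missingness is unrelated to HbA1c or related to it in the same way in both arms.

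A different pattern in each arm is plausible, because only one arm receives the new mode. The Discussion itself foresees internet-access and technical difficulties with it. If telecare patients whose control is worsening are the ones without a final value, the remaining telecare patients look better than the randomised arm. The upper limit then moves below 0.4% too easily. For a non-inferiority claim meant to inform service policy, that is the unsafe direction.

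**Working it through.** **1. The plan's own figure.** Inputs from the Sample size section: margin 0.4, power 80%, alpha 0.05 (one-sided, as in Data analysis), drop-out 20%. No SD is stated. With n = 2(1.645 + 0.842)² SD² / 0.4², an SD of 1.9 gives 279 per arm, and 279/0.8 = 349, in line with 350. Back-solving from 280 evaluable per arm gives SD = 0.4 × √140 / (1.645 + 0.842) = 1.90. At one-sided 0.025 the implied SD would be 1.69. So 350 is reachable but cannot be verified. SD 1.5 to 1.9 is used below as an assumption.

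**2. Which HbA1c values could exist.** Seven consultations 14 weeks apart fall at weeks 0, 14, 28, 42, 56, 70 and 84. Strict alternation from an onsite start puts the telecare arm onsite at weeks 0, 28, 56 and 84, and the control arm at all seven. T2 (week 42) is then a virtual visit for telecare, so the telecare blood sample nearest to T2 may fall at another week.

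**3. Size by formula.** Let m be the proportion missing in each arm. Let Δ be the gap in final HbA1c between patients without and with a value in telecare, minus the same gap in control. The observed difference is then too favourable to telecare by m × Δ. At a true difference of 0.4, with n = 350(1 − m) per arm:

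false non-inferiority = Φ( mΔ / (SD √(2/n)) − 1.645 )

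Example: m = 0.20, Δ = 1.0, SD 1.5. The SE is 1.5 × √(2/280) = 0.127; 0.2/0.127 − 1.645 = −0.07; Φ = 47%.

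| m | Δ (HbA1c points) | SD 1.5 | SD 1.9 |
|---|---|---|---|
| any | 0 | 5% | 5% |
| 5% | 1.0 | 11% | 10% |
| 10% | 0.5 | 11% | 9% |
| 10% | 1.0 | 21% | 16% |
| 20% | 0.5 | 20% | 15% |
| 20% | 1.0 | 47% | 35% |

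A negative Δ (worse patients lost from control) takes the error below 5%.

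**4. Size by simulation.** Settings: 350 per arm, true difference 0.4, SD 1.5 to 1.9, visit correlation about 0.7 to 0.75, leaving dependent on the last observed HbA1c. All dependence patterns are assumptions. False non-inferiority for the t-test on observed values:
- Random loss, or equal dependence in both arms: about 5%.
- 5% to 10% missing, dependence in telecare only: about 8% to 21% in most cases (one run reached 23%).
- 10% missing, control dependence at half the telecare log odds ratio: 8% to 10%.
- 20% missing, telecare only: about 24% to 56%. Runs with correlation up to 0.8 and odds ratios of 1.65 to 2.7 per SD gave 20% to 55%. A bias of 0.11 to 0.26 there corresponds to Δ = 0.11/0.2 to 0.26/0.2, about 0.55 to 1.3 points.
- Dependence in control only: under 4%.

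A likelihood-type estimate using the earlier values stayed near 5% in these settings, in several runs judged with its empirical standard error.

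**5. Two other mechanisms** (SD 1.2 to 1.5, 20% missing, values at T1, T2 and T3 only). When telecare drop-out followed the observed T1 to T2 worsening, the t-test gave 9.9% to 13.6% and the estimate using T1 and T2 gave 4.8% to 5.3%. When drop-out followed the unseen T3 change, both failed: 27.6% to 32.5% and 35.6% to 44.0%.

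**6. Precision.** At SD 1.5, correlation 0.7 and 20% random loss, the standard error fell from 0.13 (t-test) to 0.09 (repeated-measures estimate). As a check, complete data adjusted for baseline alone would give 1.5 × √(1 − 0.49) × √(2/350) = 0.08.

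**The case against.** A reader might infer more than the documents support, and the case against rests largely on that.

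- **Completers only.** The article does not say that only patients with a final value are analysed. A t-test can be run on imputed data, and analysis sets and missing-data methods may sit in the full protocol or SAP. That silence is no finding. What stands is the choice of a test that does not itself use earlier HbA1c.
- **20% missing.** The 20% is the top of a cited 0% to 20% range and serves to inflate the sample size. The Maintenance section lists a change of mode separately from withdrawal, so a patient who gives up telecare can stay in clinic care. Results come from the hospital database. Missing HbA1c may therefore be well below 20%, which shrinks the bias without removing the possibility.
- **Direction.** The Discussion says working patients tend to skip appointments and that telecare may prevent this. Loss could then concentrate in control and make the test conservative. The direction is open.
- **Interim values.** The article does not say that HbA1c is drawn at every onsite visit, so values at weeks 28 and 56 cannot be taken as given. Only T1, T2 and T3 are planned.
- **The remedy.** A likelihood model assumes missing at random. When drop-out followed unseen values, using earlier HbA1c did worse than the t-test.

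These points limit the size and certainty of the concern. They do not make the t-test a good match for an outcome measured repeatedly with drop-out expected.

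**Conclusion.** The concern holds in conditional form. The named test leaves baseline and interim HbA1c unused, and if final values are missing in a way that relates to HbA1c differently by arm, its result is biased. The documents do not show that this will happen or in which direction. Nor do they show that the trial will make a false claim of non-inferiority. Week 84 as the decision visit is also an inference.

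False non-inferiority at a true difference of 0.4 runs from the nominal 5% to about 24% to 56%. The upper figures need 20% missing with dependence in telecare only and should be read as the worst case. With 5% to 10% missing, about 8% to 21% is the more useful range. All figures rest on assumed SDs, correlations and drop-out patterns. The loss of precision does not depend on any drop-out pattern. The change is worth making, at moderate confidence.

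**What to change.** In the Data analysis section:

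1. Name the decision visit, for example week 84.
2. Make the primary analysis a likelihood-based repeated-measures model on all randomised patients. Use baseline and every HbA1c value in the hospital database up to that visit, including the planned T2 value and any others drawn at onsite visits, assigned to visit windows. Include arm-by-visit terms, a common baseline mean and an unstructured covariance.
3. Compare the upper one-sided 95% limit of the arm difference at the decision visit with 0.4%.
4. Keep the t-test as a sensitivity analysis, and add one that sets missing telecare values worse, for example by 0.4 points. This second analysis is needed because the model relies on missing at random.

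The cost is about a paragraph of text, definition of the visit windows and a slightly more complex model. Because the model uses whatever HbA1c is on record, the change itself requires no added blood draws or visits. The downside is the missing-at-random assumption, which the sensitivity analysis tests but does not remove.
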